**FIGURE 1 jan14953-fig-0001:**
[figure not shown]
Power and sample size over a varying range of the mean number of subjects per cluster

Overall, a higher ICC yielded a lower total number of subjects needed to achieve the desired power (Figure 1, panel b compared with a). We found the solution with 200 participants, 20 nursing homes and three steps (Figure 1a) to be optimal because three steps put much less burden on participants and study staff than a greater number of steps. On the other hand, the proposed ICCs are more conservative. Furthermore, it seems highly feasible to administer the intervention to participants in the randomized clusters within three steps. To account for attrition, we further adjusted the required sample size. Husebø et al., (2019) and Chenoweth et al., (2011) reported 20–25% attrition. We increased the number of clusters from 20 to 22 to address the risk of underpowering our study. To summarize, our study will enrol and follow 220 participants in 22 clusters over six discrete measurements (one at baseline and five during the control and intervention conditions), which will yield a total of 1320 observations. We do not intend to conduct interim analyses of the outcomes.

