### Sample size calculation

3.9

The sample size was calculated using simulations for a cohort stepped‐wedge design. The primary outcome would be repeatedly obtained from the same participants within each cluster (nursing home), as in previous similar studies (Aegerter et al., 2020). Based on previous QUALIDEM results, we assumed a baseline mean of 71.3 and a standard deviation of 16.7 (van Dam et al., 2019). The number of nursing homes was set to 20 with three cluster groups. The attributable difference in the QUALIDEM was expected to be around 5%, as derived from clinical expertise. We set the number of steps to three for practical reasons (study rollout). After baseline measurement, nursing homes will switch from the control condition to the intervention condition at given periods until all nursing homes are applying the intervention regime. To determine the appropriate sample size, we varied the average cluster size in our simulation over a range of 4 to 16 subjects per cluster. We assessed the sensitivity of the sample size calculations by varying the cluster‐specific and subject‐specific ICC. More specifically, we used ICC values for Rho[1] = {0.1, 0.2} and Rho[2] = {0.2, 0.3}, respectively. In our simulation, we used a standard closed cohort mixed‐effects model. The latter comprised a random effect for the clusters (*α*) and a random effect for the repeated measurements on the same cohort of individuals (*ζ*). Moreover, the model included a fixed effect to account for time trends (*β*) and a fixed effect representing the treatment effect (*θ*).
(1)
$$y=\mu_{\mathrm{ij}}+e_{\mathrm{ijk}}$$

(2)
$$\mu_{\mathrm{ij}}=\mu +\alpha_{i}+\zeta_{\mathrm{ik}}+\beta_{j}+X_{\mathrm{ij}}\theta$$

(3)
$$\zeta_{\mathrm{ik}}∼N\left(0,\sigma_{\zeta }^{2}\right)$$

(4)
$$\alpha_{i}∼N\left(0,\sigma_{\alpha }^{2}\right)$$

(5)
$$e_{\mathrm{ijk}}∼N\left(0,\sigma_{e}^{2}\right)$$

To estimate our models, we used the linear mixed‐effect method (lmer) from the R‐package lme4 (Bolker et al., 2021). Furthermore, we set the acceptance probability for a Type I Error to *p* = .05 and the acceptance probability for a Type II Error to *p* = .20 (power = 0.80).

The required sample sizes to achieve the desired power of 0.80, given the aforementioned parameters and assumptions, are shown in the two scenarios plotted in Figure 1.

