### Statistical analyses

3.11

The data will be analysed on an ‘intention to treat’ basis and analysed per protocol to verify the intention to treat results, as in previous similar studies (Aegerter et al., 2020). Missing data will be examined using the R‐package naniar 0.5 (Tierney, 2021) and multiple imputations will be used if required.

Linear mixed‐effects will be used to assess intervention effects on our primary outcome measured using the QUALIDEM over the study period. The broader category of generalized linear mixed‐effects models (GLMMs) will also be used to analyse secondary outcomes. GLMMs are extremely flexible since they support various distributions of the outcome variable, such as Gaussian, Bernoulli, binomial, gamma, negative binomial, ordinal and Poisson, as well as several link functions (e.g., identity, log, logit, probit and log‐log) (Cnaan et al., 1997; Lindstrom & Bates, 1990). Moreover, these models will handle non‐normal data and adjust the effects of clustering. Individuals will be nested in each cluster, and individuals will be measured at baseline and at five additional time points (Hemming et al., 2018; Luke, 2019).

Consequently, we will use GLMMs to investigate secondary outcomes, such as the symptoms and concerns of PWD. All models will be adjusted for potential confounding factors, such as age, gender, marital status, care dependence, dementia type and severity at baseline. All statistical analyses will be performed using R statistical software (R Core Team, 2020).

An alpha level of 0.05 will be accepted as significant. The results of the mixed‐effects modelling will be presented in outcome‐specific effect sizes, including the corresponding 95% confidence intervals.

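### The attrition adjustment adds 10% to the sample beside a cited 20–25% loss, and the 1320 observations are a maximum that assumes no loss

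*Protocol article*

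**What the plan says.** All the figures stand in section 3.9 (Sample size calculation), mostly in the paragraph after Figure 1.

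- **Requirement.** The solution chosen from the simulation is 200 participants in 20 nursing homes with three steps. The figure is introduced as showing "The required sample sizes to achieve the desired power of 0.80".
- **Assumptions.** "we assumed a baseline mean of 71.3 and a standard deviation of 16.7"; "The attributable difference in the QUALIDEM was expected to be around 5%, as derived from clinical expertise"; "we used ICC values for Rho[1] = {0.1, 0.2} and Rho[2] = {0.2, 0.3}, respectively". The less favourable ICC pair (0.1 and 0.2) is read here as the one behind the chosen solution, because the article calls its ICCs the more conservative ones.
- **Attrition.** The article says that the required size was adjusted further for attrition, and that two earlier studies "reported 20–25% attrition".
- **Adjustment.** "We increased the number of clusters from 20 to 22 to address the risk of underpowering our study".
- **Result.** 220 participants in 22 homes, each measured six times, "which will yield a total of 1320 observations".

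Section 3.2 describes a closed cohort and mentions no replacement of residents who leave. Section 3.11 plans a linear mixed-effects model for the QUALIDEM, with multiple imputation if required, and states: "An alpha level of 0.05 will be accepted as significant".

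**The concern.** The requirement, the attrition rate, the adjustment and the yield are given in consecutive sentences, and they do not agree. The adjustment is presented as the answer to attrition, and the only rate given is 20–25%, yet the increase is half or less of that. No reason is offered for the smaller allowance. The closing observation count then carries no attrition at all.

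A reader would take from this that 220 residents protect 80% power for the primary outcome at the cited loss. Whether they do depends on when residents leave and on how the simulation was parameterised. The article addresses neither point in relation to attrition.

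**Working it through.** **1. Head count.** This step needs no assumption beyond the article's figures.

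- Residents per home: 200/20 = 10. Enrolled: 22 × 10 = 220, an increase of 20/200 = 10%.
- Loss that brings 220 back to 200: 1 − 200/220 = 9.1%.
- Remaining at 20% loss: 220 × 0.80 = 176, which is 24 short of 200. At 25%: 220 × 0.75 = 165, which is 35 short.
- For comparison, dividing by retention gives 200/0.80 = 250 and 200/0.75 = 267. Multiplying by (1 + d) gives 240 and 250. Neither rule gives 220, and the article states no rule.

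**2. Observations.**

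- Stated total: 220 × 6 = 1320, reproduced exactly with zero loss.
- Linear dropout reaching d at month 14 (an assumed pattern): the QUALIDEM visits in Table 2 are at 0, 3, 6, 9, 12 and 14 months. The mean of t/14 is 44/84 = 0.524. The expected total is 1320 × (1 − 0.524d), which gives 1182 at d = 0.20 and 1147 at d = 0.25.
- Dropouts contribute nothing: 176 × 6 = 1056 and 165 × 6 = 990.

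**3. Power.** The model is that of section 3.9: random home effect, random resident effect, fixed time effects and one treatment effect. The standard error comes from generalised least squares, and power = Φ(5/SE − 1.96).

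Assumptions: 5% read as 5 points, SD 16.7 as the total SD (variance 278.9), Rho 0.1/0.2, two-sided 0.05, six visits, homes split 8/7/7. The article does not say how Rho[2] enters, so two readings are shown:

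- *Total within-resident correlation:* home variance 27.9, resident variance 27.9, residual 223.1.
- *Added component:* home variance 27.9, resident variance 55.8, residual 195.2.

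| Case | Rho[2] total | Rho[2] added |
|---|---|---|
| 20 homes × 10, no loss (the article's own case) | 0.79 | 0.84 |
| 22 × 10, no loss | 0.83 | 0.88 |
| 22 × 10, linear dropout 20%, all scores used | 0.79–0.80 | 0.84–0.85 |
| 22 × 10, linear dropout 25%, all scores used | 0.78–0.79 | 0.83–0.84 |
| 22 × 10, 20% contribute nothing | 0.75 | 0.80 |
| 22 × 10, 25% contribute nothing | 0.72 | 0.77 |

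The first row reproduces the stated 0.80 at 200 residents, most closely under the total reading. In the linear-dropout rows, the lower value counts the QUALIDEM visit at the crossover month as control and the higher value counts it as intervention.

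**The case against.** The strongest reply is that a resident who leaves part-way is not lost to the analysis. The planned mixed model uses every score obtained, and residents must be present in the home at the start, so most would give at least a baseline score. With gradual dropout, power is 0.78–0.85, at worst about two points below target. This stands, and it is why the available-data figure should lead. It does not remove the mismatch, because the article does not make this argument and the simulation it describes has no dropout. A baseline score alone also helps little: under the total reading, losing 20–25% straight after baseline gives 0.75–0.72, the same as complete loss.

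It can also be said that the 20–25% comes from other studies and is not formally adopted for this trial, and that the article claims only to address a risk. That is fair as to wording. It is nevertheless the only rate given, and it is given as the ground for the adjustment.

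Three stronger readings are not supported:

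- *The trial needs 250 to 267 residents.* The article sets no target for completers and no division by retention, and that rule ignores partial follow-up.
- *1320 observations cannot occur.* It is the scheduled maximum; the fault is only that it is presented as the yield.
- *220 residents protect power against 9% loss and no more.* The 9.1% is a head count. Under the added-component reading, 22 homes still reach 0.80 when 20% contribute nothing.

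**Conclusion.** The inconsistency holds. A 10% increase offsets a 9.1% loss in head count, and the cited 20–25% would leave 176–165 residents against a stated requirement of 200. The figure of 1320 is a maximum. These counts do not depend on the ICCs, the effect size or Figure 1, which is not shown.

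The effect on power is smaller and conditional: about 0.78–0.85 with gradual loss and all available scores, and about 0.72–0.80 if 20–25% contribute nothing. A reader might infer that the trial is seriously underpowered because of attrition, but the documents do not support that, since under gradual loss power stays close to 0.80.

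The power figures rest on the assumptions listed with them. Others move the level: reading 5% as a relative change (0.05 × 71.3 = 3.57 points) gives about 0.51 at 20 × 10 under the total reading, before any attrition. That does not reproduce the article's 0.80, so it is not used here. This is a reporting error in a core figure that is cheap to correct, and not a flaw that calls for a different design.

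**What to change.** Keep 22 homes and 220 residents, and change section 3.9 as follows:

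1. State that the increase from 200 to 220 is 10% and does not by head count cover the cited 20–25%.
2. Rerun the existing simulation with a stated dropout pattern and report power at 20% and 25% attrition. Make the analysis of all available scores the main case, and residents who contribute nothing the sensitivity case. State how Rho[2] enters the model and whether 5% means 5 points.
3. Label 1320 as the maximum and add the expected number: about 1147–1182 with linear dropout, and 990–1056 if dropouts contribute nothing.

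The cost is one simulation rerun, a few reworded sentences and a slightly less favourable stated power. Enrolment, design and primary analysis do not change.

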### Validity and reliability

3.10

The allocation of a nursing home to a group will be concealed from the researchers and nursing home management during the recruitment phase. Depending on local schedules for staff rotation and planning, the cross‐over date (from control to intervention) will be communicated to the intervention nurse and nursing home to allow for scheduling case studies during the intervention. Blinding participants to the intervention will not be possible due to the intervention nurse visits and scheduling of the case studies.

Introductory sessions for all nurses and family members in all nursing homes will be conducted by the same members of the study team and the intervention nurse to avoid any teaching bias. A clinical champion will be allocated to ensure data quality in terms of completeness of data and completion pattern (Bausewein et al., 2018).

The QUALIDEM and IPOS‐Dem questionnaire responses will be anonymized and entered into an electronic case reporting form (eCRF) using REDCap electronic data capture tools hosted at HES‐SO, School of Health Valais, Switzerland (Harris et al., 2009, 2019). The original papers will remain in the nursing home.

The eCRF will consist of forms and data entry fields that allow capturing of single events and visits. Data will be entered by the trained family members, clinicians and study personnel. eCRF data entry fields will be created that only allow data to be entered in a specific format (e.g., date fields and number fields). Automated checks implanted in the eCRF will check the data for plausibility and completeness while it is being saved. REDCap is a browser‐based software that will give continuous feedback to the person entering the data (e.g., erroneous or missing data). All data will be subject to monitoring by an independent reviewer.

### Statistical analyses

3.11

The data will be analysed on an ‘intention to treat’ basis and analysed per protocol to verify the intention to treat results, as in previous similar studies (Aegerter et al., 2020). Missing data will be examined using the R‐package naniar 0.5 (Tierney, 2021) and multiple imputations will be used if required.

Linear mixed‐effects will be used to assess intervention effects on our primary outcome measured using the QUALIDEM over the study period. The broader category of generalized linear mixed‐effects models (GLMMs) will also be used to analyse secondary outcomes. GLMMs are extremely flexible since they support various distributions of the outcome variable, such as Gaussian, Bernoulli, binomial, gamma, negative binomial, ordinal and Poisson, as well as several link functions (e.g., identity, log, logit, probit and log‐log) (Cnaan et al., 1997; Lindstrom & Bates, 1990). Moreover, these models will handle non‐normal data and adjust the effects of clustering. Individuals will be nested in each cluster, and individuals will be measured at baseline and at five additional time points (Hemming et al., 2018; Luke, 2019).

Consequently, we will use GLMMs to investigate secondary outcomes, such as the symptoms and concerns of PWD. All models will be adjusted for potential confounding factors, such as age, gender, marital status, care dependence, dementia type and severity at baseline. All statistical analyses will be performed using R statistical software (R Core Team, 2020).

An alpha level of 0.05 will be accepted as significant. The results of the mixed‐effects modelling will be presented in outcome‐specific effect sizes, including the corresponding 95% confidence intervals.

### Ethical considerations

3.12

This trial was registered at the German clinical trials register (DRKS00022339). The full registration can be accessed online at http://www.drks.de/DRKS00022339. The Zürich cantonal ethics board, as the lead board, reviewed the protocol, consent forms, educational material and eCRF (BASEC‐ID: 2019‐01847). The trial's scientific content and compliance with applicable research regulations (European Medicines Agency et al., 2016; World Medical Association, 2013) was confirmed. The ethics board in Zürich will coordinate with other cantonal boards in this multicentre study. The sponsor, the ethics committee or an independent trial monitor may visit the clinical and research sites for quality assurance. All involved parties are required to keep all participant data strictly confidential. In the event of an audit by a local or cantonal ethics committee, all source data, eCRFs and raw data will be made available to the auditors by the study team.

All raw data will be handled with the utmost discretion and will remain accessible to authorized personnel who require the data to fulfil their duties within the scope of the study only. On all documents and eCRFs, participants will only be identified by unique participant numbers. Source data will be kept at the clinical sites and will remain within the nursing homes. During a monitoring visit, eCRFs on an encrypted memory stick will be handed to the corresponding clinical site where the monitoring is to be conducted.

## DISCUSSION

4

Currently, frontline staff in Swiss nursing homes need help for timely screening and reporting of needs and concerns observed in PWD (de Wolf‐Linder et al., 2018). When caring for PWD, they may observe complex and interrelated symptoms. Frontline staff needs to interpret, address and manage observed needs and concerns with an interprofessional team. Therefore, frontline staff need time and support to reflect and plan interactions, care or symptom management with other people, preferably also oriented to the person with dementia (Goodman et al., 2016). Furthermore, family members can provide valuable input and context for frontline staff to caring for the PWD and vice versa (Backhaus et al., 2020; Ellis‐Smith et al., 2018; Robertson et al., 2019).

In reviewing the literature, no research describing the symptoms and concerns and its management, be it palliative or curative, of PWD living in Swiss nursing homes is reported (Federal Council & Federal Office for Public Health, 2020). The Swiss federal office for public health (FOPH) and Swiss Alzheimer Society (2020) promote models for family member involvement for nursing homes, although frequency and form of exchange and participation are not determined and heavily based on family information provision members. FOPH made no specific recommendation for assessment and screening instruments for frontline staff other than the routine instruments. The relevant German guideline (Deuschl & Maier, 2016) refers to the nurse observation scale for geriatric patients (NOSGER) (Brunner & Spiegel, 2002), a scale for nurses to observe and rate behaviour that challenges, social behaviour, mood and functional impairment. However, neither NOSGER nor any of the routine assessment instruments reflect the person‐centred approach integral to palliative care, person‐centred care and caring quality in PWD (Lynette Chenoweth et al., 2019; Etkind et al., 2015; Howell et al., 2013). With IPOS‐Dem, a promising model for multi‐dimensional needs and concern assessment, improved communication, and improved caring quality, quality of care and quality of life in PWD has been described and identified (Ellis‐Smith et al., 2018).

Therefore, we propose to evaluate a novel case studies intervention based on accessible systematic observation of needs and concerns by family members and frontline staff. The case studies intervention is conducted by an expert nurse external to the nursing home, trained to encourage open discussion and bottom–up management needs and concerns in PWD participating in the study. We expect to encounter heterogeneity in Swiss nursing homes regarding the needs and concerns of PWD and organization, leadership, staffing and grade mix. Therefore, to account for the complexity of the intervention, we planned the study with an SW‐CRT design. SW‐CRTs have been shown to work well in the exploratory phase of developing complex interventions (Craig et al., 2008).

On the one hand, our decision to conduct an SW‐CRT reconciles the practical ethical and logistical concerns another trial may have posed for the PWD, us and the nursing home managers involved and the research team. On the other hand, there are drawbacks to employing this design: an SW‐CRT usually requires a larger sample size than the corresponding designs; also with the staggered starting times, the study duration is increased (Haines & Hemming, 2018; Hemming, Haines, et al., 2015). However, since blinding frontline staff and family members (i.e., the outcome assessors) is not possible in our study, we proceed with utmost care to reduce the risk of bias (Hemming et al., 2018; Siebenhofer et al., 2018). The increased sample size and, therefore, nursing homes contribute data on both intervention and control condition. The resulting datasets will be made accessible to interpret and apply to international long‐term care contexts.

## CONCLUSION

5

This SW‐CRT will evaluate the effect of frontline healthcare staff and family members performing repeated structured assessment and subsequent case studies on the caring quality, symptoms and needs of PWD. Implementing the IPOS‐Dem may further encourage routine usage of outcome measures and foster more excellent staff–family communication. The use of the IPOS‐Dem will empower frontline staff in nursing homes and family members to report their insights about PWD. Furthermore, case studies led by specialist nurses and based on IPOS‐Dem‐informed professional and family input may improve quality of life and ameliorate the needs and concerns of PWD.

## DATA AVAILABILTY STATEMNT

6

After Embargo for publications, the anonymized dataset will be made available on https://doi.org/10.5281/zenodo.4008427. We provide the statistical code under https://doi.org/10.5281/zenodo.4008429.

### PEER REVIEW

The peer review history for this article is available at https://publons.com/publon/10.1111/jan.14953.
